**Figure 1 F1:**
[figure not shown]
Sample size calculation used for this clinical research.

**Figure 2 F2:**
[figure not shown]
Determination of the sample size for this clinical research.

#### Experimental groups

3.1.9

The experimental groups are described according to the Table 1.

**Table 1 T1:**
[figure not shown]
Experimental groups are described as shown below.

#### Use of low-level laser for aPDT

3.1.10

For the use of the aPDT, the light source will be a low-level laser pen in the visible red band, a semiconductor (GaA1As and InGaA1P), The Laser DUO continuous mode, model from MM Optics, 100 mW, 2471/cm^2^, 148 J/cm^2^, irradiance 2471 mW/cm^2^. The device will be calibrated (*λ* = 660 nm, 6 J, 60 s), per spot.

The sessions will be held at the pediatric dentistry clinic. The volunteer and operator will be the only individuals present. Eye protection will be worn by both. The active tip of the laser will be covered with plastic wrap (PVC) for hygiene purposes and to avoid cross-contamination. The operator will be duly garbed. Based on a study by Guglielmi et al,^[8]^ the laser will be applied at a single point in contact with the cavity for each carious lesion. A conventional tip will be used and eye protection will be worn throughout the entire irradiation procedure to ensure the complete isolation of the patient's eyes.

As a randomized clinical trial, the recommendations of the Consolidated Standards of Reporting Trials^[36]^ will be used for greater transparency and quality.

#### Procedures

3.1.11

Training and calibration of operator and examiner: All treatments will be performed by a single examiner who will undergo a training and calibration exercise in the initial phase of the study involving teeth randomly allocated to 2 groups. The operator will perform the treatment and a previously trained examiner will perform a clinical evaluation of the removal of carious tissue. The examiner will be unaware of the technique applied to the teeth (blind study). The previously trained examiner will evaluate all cavities after the respective interventions and will test the hardness of the remaining dentin. For carious tissue to be considered removed, there must be agreement between the operator and the examiner. This pilot study will be conducted to determine interexaminer agreement regarding the clinical and radiographic evaluations by examiners having undergone a calibration exercise with the calculation of Kappa coefficients. Interexaminer agreement must be greater than 85% (*K* > 0.85).

Randomization: The type of treatment will be determined based on the identification of the lottery stone:

Number 1 – Traditional caries removal with a low-speed drill (Group 1).

Number 2 – Removal of carious tissue around cavity walls with dentin curette, aPDT with PapacarieMBlue administration of PapacarieMBlue modified with MB followed by aPDT (Group 2).

Next, the individual and tooth will receive the previously determined treatment. Likewise, another tooth in the same individual will receive the treatment that was not determined previously.

Blinding: The clinical evaluations of the carious tissue removal, as well as the microbiological and radiographic analyses, will be performed by examiners blinded to the treatments performed on each tooth.

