Studies have demonstrated that antimicrobial photodynamic therapy (aPDT), have also been developed for the treatment of dental caries.^[22–27]^ The photodynamic action occurs when a photosensitizing agent absorbs photons from the light source and its electrons enter an excited singlet state.^[28]^ Different classes of chemical compounds, such as phenothiazines, phthalocyanines, and porphyrins, which have photoactive properties, have been effective in aPDT.^[23–26,28–32]^ Light must interact with the tissue in order to produce biological effect. The use of a chromophore applied to dentinal tissue has the function of absorbing light radiation, thereby increasing the interaction of the light with the tissue.^[22,23]^

Methylene blue (MB) is a widely known histological dye that has been in use for many years.^[33]^ It belongs to the phenothiazinium class of compounds. It is an amphiphatic tricyclic planar cationic molecule with 1 intrinsic quarternary nitrogen atom, and it presents phototoxic efficiency.^[34,35]^ Due to its photochemical and photobiological characteristics, widespread availability and ability to be excited with light, the aim of adding MB to the gel is to potentiate the antimicrobial action of aPDT.

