#### Trial design

3.1.3

Randomized, controlled, blind, clinical trial

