#### Clinical evaluation

3.1.16

The clinical evaluation will be performed by researcher blinded to the different treatment groups. The criteria used of the evaluation will be the retention of the restorative material in the cavity and the occurrence of secondary caries. The evaluation scores will be based on the results of previous studies.^[4]^ Digital photographs of the restorations will also be taken and serve to complement the clinical and radiographic findings. The visual demonstration will contribute to any necessary clarifications and facilitate the discussion and documentation of the cases. Thus, digital photographs will be taken (camera: Canon Sx500 IS) of all teeth in the different groups before and after the interventions.

0 = present; no defects;1 = present; small marginal defects measuring less than 0.5 mm in depth; no need for repair;2 = present; small marginal defects measuring 0.5 mm to 1 mm in depth; need for repair;3 = present; large marginal defects measuring 1 or more mm in depth; need for repair;4 = absent; restoration nearly or completely lost; need for treatment;5 = absent; additional treatment having been performed for some reason;6 = tooth absent for any reason;7 = present; surface wear measuring less than 0.5 mm in depth; no need for replacement;8 = present; surface wear greater than 0.5 mm in depth; need for replacement;9 = impossible to diagnose.

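### The caries-removal assessment is called blinded, but the examiner probes an open cavity that differs by arm, and the verdict needs the consent of the operator who gave the treatment

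*Protocol article*

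**What the plan says.** Trial design (3.1.3) labels the study "Randomized, controlled, blind, clinical trial".

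Procedures (3.1.11) divides the roles: "The operator will perform the treatment and a previously trained examiner will perform a clinical evaluation of the removal of carious tissue". It then says of the assessor: "The examiner will be unaware of the technique applied to the teeth (blind study". The assessor's task follows: "The previously trained examiner will evaluate all cavities after the respective interventions and will test the hardness of the remaining dentin". The next sentence sets the decision rule: "For carious tissue to be considered removed, there must be agreement between the operator and the examiner". After that the paragraph turns to a pilot study of agreement, measured by Kappa. A separate Blinding paragraph in the same section repeats that the evaluation of caries removal, like the microbiological and radiographic analyses, is made by examiners who do not know the treatment.

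Interventions (3.1.7) gives the order of steps. In both groups, probing of the remaining dentin is step 7 and the glass ionomer restoration is step 8. Group 1 is treated with carbide burs and manual instruments. Group 2 has the methylene blue gel in place for 5 minutes, curettage of the lateral walls only, no removal on the pulp floor, and then irradiation.

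**The concern.** A texture or hardness judgement made with a probe is subjective. Blinding protects it only if the assessor cannot tell the arms apart and nobody who knows the arm can change the result. Here both conditions are doubtful. What the examiner inspects differs between arms by design, and the agreement rule gives an unblinded person a say in the recorded verdict.

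Two measures are at stake. One is the verdict that caries has been removed. The other is procedure time, which section 3.1.14 measures from the start of treatment until removal is complete. If that end point is declared under the agreement rule, the time inherits the same weakness. A reader of the eventual report would take both as coming from a blinded assessment.

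**Working it through.** The plan gives no figure on this point, so the check sets the sections side by side. The only count used is 16 teeth per group (3.1.8), hence 16 + 16 = 32 cavities, which matches Participants (3.1.4).

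**Step 1: is the cavity open when it is assessed?** Yes. Step 7 precedes step 8 in both groups. A hardness test of remaining dentin is also possible only before the restoration covers it.

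**Step 2: do the arms look or feel different then?**

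| Feature at step 7 | Group 1 | Group 2 |
|---|---|---|
| Cutting | Carbide burs and manual instruments | Non-cutting curette |
| Lateral walls | Carious dentin removed | Carious tissue removed |
| Pulp floor | No instruction to leave caries | Caries left in place |
| Dye | None | Methylene blue gel for 5 minutes |

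The pulp-floor row follows directly from the intervention text. The property being tested, the hardness of what remains, is therefore the property on which the arms differ by design. The dye row points the same way, since the Introduction says "Methylene blue (MB) is a widely known histological dye", but lasting colour in the dentin is an inference. No masking step is described.

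**Step 3: do paired teeth add to this?** Procedures gives another tooth of the same child the treatment not drawn for the first. Where a child contributes both teeth, recognising one arm reveals the other.

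**Step 4: what does the agreement rule do?** Let E = 1 if the examiner rates the caries as removed, and O = 1 if the operator does. Even if the two rate separately, a tooth counts as removed only when both are 1:

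P(removed) = P(E = 1) × P(O = 1 | E = 1).

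Suppose the examiner were perfectly blind and P(E = 1) were the same value p in both arms. The difference between arms would then be

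p × (q1 − q2),

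where q1 and q2 are the operator's rates of concurring in Groups 1 and 2. The operator knows the arm, so nothing in the design holds q1 equal to q2. If discussion is allowed before the ratings are fixed, E can move as well. The documents give no value for p, q1 or q2, so no size or direction follows.

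**Step 5: does the rule apply to the trial or only to the pilot?** The sentence stands in the training and calibration paragraph, and the pilot is named directly after it. The sentence before it covers all cavities after their interventions, and the Blinding paragraph lists the same evaluation with no pilot limit. The trial reading is the more natural one, but the text does not settle it.

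**Step 6: can the criterion be met in Group 2?** If removal includes the pulp floor, a Group 2 tooth treated as instructed cannot meet it, and the timing end point in 3.1.14 is never reached. If removal means the walls only, the text does not say so. The criterion and the Group 2 instruction must be reconciled.

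**The case against.** The case on the other side has real force in several places.

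- **The verdict is not a main endpoint.** The sample size rests on colony counts. The clinical follow-up criteria in 3.1.16 are retention of the restoration and secondary caries. Statistical analysis (3.1.17) names no comparison of removal verdicts. This stands, and it limits the stake.
- **Agreement may mean two separate ratings that coincide.** The Kappa language nearby supports this. On that reading the operator alone cannot declare success. The operator can still withhold it, as Step 4 shows, so the verdict still depends on an unblinded person.
- **The rule may be pilot-only.** This is possible. It calls for clarification and does not touch the point about the open cavity.
- **A condensed article may omit a masking step.** It may. The concern rests on stated text that conflicts, and one added sentence would answer the part about the cavity.

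Four stronger readings are tempting, and the documents do not support them.

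- A reader might infer that the dye makes blinding impossible. The text never says that dentin stays stained after the gel, the curettage and the second sample.
- A reader might see a clash with "The volunteer and operator will be the only individuals present". That sentence stands among the laser safety instructions and need not exclude an examiner who comes in afterwards.
- A reader might fear that photographs reveal the arm at follow-up. The text is "Digital photographs of the restorations will also be taken and serve to complement the clinical and radiographic findings", and no open-cavity photograph is described. Restoration is itself a step of each intervention, so a picture taken afterwards most naturally shows the restored tooth.
- A reader might conclude that the whole trial is unblinded. Nothing here shows that for the laboratory counts, the scanned density or the follow-up scoring.

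**Conclusion.** The concern holds within limits. The open-cavity assessment of caries removal is unlikely to be blind in practice. Under the agreement rule its recorded result would not be a blinded one in any case.

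Up to 32 cavities are concerned for the examiner's view of the cavity, and the same number for the agreement rule if it applies to the trial. The affected measures are the removal verdict and, if the clock stops at that verdict, procedure time.

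The conclusion assumes that the probing at step 7 is the examiner's hardness test and that no undescribed masking is used. The change should be made because it costs almost nothing. The point does not put the microbiological or radiographic comparison in doubt.

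**What to change.** 1. In 3.1.11, have the examiner record texture and hardness alone, before any exchange with the operator. Make that record the one analysed. Keep the operator's rating only to report agreement. Any clinical decision on completing the procedure stays as it is.
2. State whether the agreement rule applies to the pilot, to the trial or to both.
3. State that the open-cavity assessment is not reliably blinded. Restrict the blinding claim to the microbiological and radiographic readings, with tubes and films identified by code only, and to the follow-up scoring.
4. Reconcile the criterion for removal, and the end point of procedure time in 3.1.14, with the Group 2 instruction on the pulp floor.

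The cost is wording in sections 3.1.3, 3.1.11 and 3.1.14, one extra recorded rating per tooth, and coded labels where these are not already used. No extra staff or teeth are needed. The downside is a more modest blinding claim.

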#### Microbiological evaluation

3.1.12

A sample of infected dentin will be taken from each selected tooth before the removal of the carious tissue. The samples will be standardized with the use of a Meyhoefer auricular curette n° 2 and placed into test tubes containing 3.8 ml of transport medium (phosphate buffered saline; Labcenter, São Paulo, Brazil). The dental biofilm will be dispersed in the transport tube containing glass pearls through agitation at maximum speed in a vortex device for 30 seconds to homogenize the biological material. Next, the biofilm will be diluted in series on the order of 10^1^ to 10^6^ in peptone water and inoculated in culture media in Petri dishes. Aliquots of dilutions 10^4^, 10^5^, and 10^6^ will be sewn on the surface of Brucella agar (Difco, Kansas City) containing defibrinated sheep blood (50 ml/L), hemin (Inlab, São Paulo, Brazil) (5 mg/ml), and menadione (Inlab) (10 mg/ml) for the determination of the total number of viable microorganisms (VM). Aliquots of dilutions 10^3^ and 10^4^ will be sewn on Mitis Salivarius agar (Difco) for the determination of the total number of streptococcus (S). Aliquots of dilutions 10^1^ and 10^2^ will be sewn on Mitis Salivarius agar with the addition of debacitracin for the determination of the population of streptococcus of the mutans group (SM).^[34]^ Aliquots (100 μl) from each dilution will be sewn onto the surface of agar and spread with the aid of a Drigalski spatula. Undiluted aliquots and aliquots from dilution 10^2^ (100 μl) will be pour plated on Rogosa SL agar (Difco) for the determination of lactobacilli (LB)_._ The Brucella agar dishes will be incubated in an anaerobic chamber (PLAS by LABS, Lansing, MI) at 37°C for 7 days. The Mitis Salivarius agar and Mitis Salivarius Bacitracin dishes will be incubated in a 10% CO_2_ atmosphere (CO_2_ greenhouse, Shel Lab, mod. 2123, Oregon) at 37°C for 48 hours. The dishes containing Rogosa agar will be incubated in a 10% CO_2_ atmosphere at 37°C for 72 hours_._ After incubation, the characteristic colonies in each dish will be counted with the aid of a stereomicroscope at a magnification of 10 times in dilutions with 30 to 300 colonies per dish. All procedures will be performed in duplicate and the mean of the counts will be calculated. The results will be expressed in CFU of SM and LB as well as in proportion of streptococcus (% S/VM), SM group (% SM/VM and lactobacilli (% LB/VM) in relation to the total of VM. For SM, the proportion in relation to the total of streptococci (% SM/S) will also be calculated.^[37]^

Immediately after the removal of the carious tissue, samples of the remaining dentin will be taken with a Meyhoefer auricular n° 2 curette and the aforementioned procedures will be repeated.

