## Introduction

1

Dental caries remains a public health problem throughout the world and develops as the result of a dynamic process mediated by acid produced by cariogenic bacteria, leading to the loss of dental tissue.^[1]^ Minimal intervention combined with knowledge regarding the development of dental caries has led to major transformations in the restorative treatment paradigm, with a striking change involving the maximal preservation of sound dental tissue capable of remineralization.^[2,3]^

The partial removal of dental caries with the aim of maintaining the integrity of the pulp is currently considered the treatment of choice for deep carious lesions provided that certain diagnostic principles are respected.^[3–5]^ With minimally invasive clinical treatment using different procedures,^[6,7]^ the most superficial layer of infected dentin, which is irreversibly denatured and not capable of re-mineralization, is removed.^[5–8]^ The more internal or “affected” dentin is reversibly denatured and capable of remineralization and should be preserved.^[3,9–11]^ Thus, various aspects are important to the indication and performance of these procedures, such as the defense mechanism of the dentin-pulp complex in the occurrence of dental caries, the initial diagnosis, the differentiation of the types of dentin that compose the carious lesion, and the materials indicated for application to the remaining dentin.^[12–14]^

Papacarie^TM^ is a gel composed of papain and chloramines.^[3,15,16]^ The latter has disinfectant quality and the former is an enzyme similar to human pepsin that acts as a debriding agent that does not harm sound tissue and accelerates the healing process; papain also has bactericidal, bacteriostatic, and anti-inflammatory properties.^[17–19]^ Thus, it is associated with minimally painful treatment for caries lesions from primary teeth^[20,21]^ and exerts a positive result in bacterial reduction.^[21]^

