#### Interventions

3.1.7

Group 1 – Caries removal with a low-speed drill.

1.Initial periapical and interproximal radiographs with double films;2.Prophylaxis with toothbrush and fluoride toothpaste;3.Relative isolation with lip bumper, cotton roll, and aspirator;4.Microbiological sampling with ear curette for standardization of volume of carious tissue;5.Removal of carious dentin with carbide burs and manual instruments;6.Additional microbiological sampling;7.Clinical inspection of texture of remaining dentin with an exploratory probe;8.Restoration with glass ionomer cement (Ketac Molar EasyMix – 3M ESPE);9.Clinical and radiographic follow-up.

Group 2 – Removal of carious tissue around cavity walls with dentin curette, administration of PapacarieMBlue modified with MB and aPDT.

1.Initial periapical and interproximal radiographs;2.Relative isolation with lip bumper, cotton roll, and aspirator;3.Microbiological sample with otoscope curette to standardize volume of carious tissue;4.Application on PapacarieMBlue (addition of MB) for 5 minutes as a preirradiation time to potentiate effect of aPDT; removal of carious tissue around lateral walls of the cavity with noncutting curette; no removal of carious tissue on pulp floor;5.Irradiation of dental tissue for 1 minute on a single point;6.Second microbiological sample of remaining dentin with curette;7.Clinical evaluation by inspection of texture of remaining dentin with exploratory probe;8.Restoration with glass ionomer cement (Ketac Molar EasyMIx 3M ESPE);9.Follow up;10.Radiographic control: periapical and interproximal radiographs at 3, 6, and 12 months.

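### All dentin samples go into plain buffered saline with no neutraliser, so any active chloramine carried over from the gel would lower only the Group 2 post-treatment counts

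*Protocol article*

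**What the plan says.** In the protocol article, section 3.1.12 (Microbiological evaluation), each sample is "placed into test tubes containing 3.8 ml of transport medium (phosphate buffered saline; Labcenter, São Paulo, Brazil". It is then vortexed, serially diluted in peptone water and plated. The post-treatment sample is handled in the same way: "samples of the remaining dentin will be taken with a Meyhoefer auricular n° 2 curette and the aforementioned procedures will be repeated".

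Section 3.1.7 (Interventions) gives the Group 2 sequence. Step 4 is "Application on PapacarieMBlue (addition of MB) for 5 minutes as a preirradiation time to potentiate effect of aPDT", with curettage of the lateral walls and "no removal of carious tissue on pulp floor". Step 5 is irradiation. Step 6 is "Second microbiological sample of remaining dentin with curette". No step between 4 and 6 removes the gel. In Group 1 the tissue removed between the two samples is taken out with burs and hand instruments, and no antimicrobial agent is listed.

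The Introduction describes the gel as papain plus chloramines. Of the chloramines it says "The latter has disinfectant quality", and it credits papain with bactericidal and bacteriostatic properties.

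The plating dilutions differ by organism. Total viable counts use 10^4 to 10^6, total streptococci 10^3 and 10^4, and mutans streptococci 10^1 and 10^2. For lactobacilli, "Undiluted aliquots and aliquots from dilution 10^2^ (100 μl) will be pour plated on Rogosa SL agar".

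**The concern.** The count is meant to measure what survived in the cavity. If an antimicrobial enters the tube with the sample and the medium does not stop it, the count also includes what died afterwards. By the protocol's own description of the gel, that can happen in one of the four kinds of sample only: Group 2, post-treatment. Any such loss therefore goes one way, and it enters both the before-after comparison in Group 2 and the comparison between groups.

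The usual safeguards do not help. Baseline samples precede the gel, so adjusting for them removes nothing. Blinding of the microbiological analysis (3.1.11) cannot stop a chemical effect. Duplicate plating repeats the same loss.

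CFU is the quantity behind the sample size (3.1.8), and the antimicrobial effect is specific objective 2 (3.1.2). The organisms to be reported directly as CFU, mutans streptococci and lactobacilli, are also those plated at the lowest dilutions.

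**Working it through.** **1. The plan's own figure.** Section 3.1.8 states 16 teeth per group, for paired samples with 1.96 and 0.84. The expected difference and SD are not in the text and the figures are not shown, so 16 cannot be reproduced. It can be solved backwards:

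n = ((1.96 + 0.84) / d)², so d = 2.80 / √16 = 0.70 SD of the paired differences.

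The point concerns the assay and does not change this number. It is used only in step 5.

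**2. Which samples can contain gel.**

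| Sample | Gel applied before sampling? | Medium |
|---|---|---|
| Group 1, before | No | Buffered saline |
| Group 1, after | No | Buffered saline |
| Group 2, before | No | Buffered saline |
| Group 2, after | Yes | Buffered saline |

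**3. Dilution of any carried gel.** The tube holds 3.8 ml = 3,800 µl (3.1.12). The carried volume v is an assumption, shown from 1 to 50 µl. Tube dilution = (3,800 + v) / v.

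| v (µl) | Tube, and undiluted lactobacilli aliquot | Mutans aliquot (10^1) | Total streptococci aliquot (10^3) | Total viable aliquot (10^4) |
|---|---|---|---|---|
| 1 | 1:3,801 | about 1:38,000 | about 1:3.8 million | about 1:38 million |
| 10 | 1:381 | about 1:3,800 | about 1:380,000 | about 1:3.8 million |
| 50 | 1:77 | about 1:770 | about 1:77,000 | about 1:770,000 |

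These are strengths in the aliquot. A 100 µl aliquot poured into agar is diluted again. Assuming 15 ml of agar, the factor is (15 + 0.1) / 0.1 = 151. Gel in the lactobacilli plate is then about 1:12,000 (77 × 151) at 50 µl and about 1:570,000 (3,801 × 151) at 1 µl. Plate carry-over is therefore small even for lactobacilli, and negligible for total viable counts and total streptococci. Contact in the tube comes before any dilution and applies to all four counts.

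**4. What a loss would do to the count.** If a fraction L of the surviving bacteria is lost after sampling, the apparent log10 reduction rises by −log10(1 − L):

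- L = 10%: 0.05
- L = 50%: 0.30
- L = 90%: 1.00

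This converts a loss into log units. It does not estimate L, which the documents do not allow.

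**5. What it could do to the test.** Take no true difference between groups, 16 pairs, a normal approximation, and a bias b in SD of the paired differences. The two-sided rejection probability is Φ(4b − 1.96) + Φ(−4b − 1.96).

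| Bias as share of 0.70 | b | Rejection probability |
|---|---|---|
| 0% | 0 | 5% |
| 10% | 0.070 | 6% |
| 25% | 0.175 | 11% |
| 50% | 0.350 | 29% |
| 100% | 0.700 | 80% |

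The shares are illustrative. The table shows how sensitive a comparison of this size is to a one-sided artefact, not how large the artefact is.

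**The case against.** The other side has a good case on how much can be inferred.

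- A reader might infer that the sample certainly comes from dentin still covered in gel. The documents do not show this. The Group 2 list also mentions no cleaning before the dentin is probed or the glass ionomer is placed, and Group 1 lists no cavity cleaning either. The list is condensed, and the sample is described as remaining dentin, not gel.
- A reader might infer that the agents stay active in the tube. This is not shown either. Gel strength, carried volume and holding time are absent, and the Introduction describes the properties of the product as applied, not at a dilution of 1:77 or 1:3,801.
- Plate carry-over is easily overstated. As the working shows, it matters at most for lactobacilli and mutans streptococci.
- The dye is described as acting when it absorbs light, and nothing says that the tubes or plates are lit to any effect.
- The pilot in 3.1.11 covers agreement on the clinical and radiographic evaluations. It has no microbiology component, so a bench check cannot be counted as already provided for.

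All five points stand, and they limit the claim. They do not remove it. The transport medium is not a detail left out for brevity: the article names it, with volume and supplier, and no neutralising agent is part of it. The agent is in one group only, so the direction of any effect is fixed even though its size is unknown.

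**Conclusion.** The point holds as a one-sided risk of bias, not as a demonstrated bias. It rests on two conditions that the documents leave open: that some gel reaches the tube, and that its chloramine is still active there. If both are met, the Group 2 post-treatment CFU is too low and aPDT looks better than it is. The main route is contact in the tube before dilution. Plate carry-over is a minor addition for two organisms, and the dye matters only with light exposure.

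The size cannot be derived. The figures of 0.30 log10 per halving of recovery, and of 11% or 29% false positives if the artefact reached a quarter or a half of the implied detectable effect, are conditional illustrations. It would go too far to call a positive CFU result a laboratory artefact. What can be said is that, as described, the assay could not separate killing in the cavity from killing in the tube. The point deserves a change because that change is cheap and the analysis cannot repair the problem afterwards.

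**What to change.** In 3.1.12, replace the plain saline with a transport medium that contains a chloramine neutraliser. Use it for all samples, before and after treatment and in both groups, so that handling stays identical. State that tubes and plates are protected from light until incubation.

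Optionally, confirm the choice with a small bench recovery check: known CFU placed in the new medium, with and without gel, then plated as planned. The arm without gel, set against plain saline, shows whether the medium itself reduces recovery. The arm with gel shows whether any activity remains, including from papain, which a chloramine neutraliser may not address. This is separate laboratory work and not part of the agreement pilot in 3.1.11.

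The cost is a change of medium, evidence that it does not lower recovery, light-proof storage and a little bench time. No treatment step, visit, patient number or sample-size figure changes.

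### The plated dilutions and the 30–300 colony rule leave a ten-fold range of lactobacilli counts with no countable dish, and set a floor on the total count that also caps two reported percentages at 10%

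*Protocol article*

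**What the plan says.** Everything needed is in the Protocol article, section 3.1.12 (Microbiological evaluation).

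- **Counting rule.** Only dishes in one window are read; colonies are "counted with the aid of a stereomicroscope at a magnification of 10 times in dilutions with 30 to 300 colonies per dish".
- **Volume.** For the surface plates: "Aliquots (100 μl) from each dilution will be sewn onto the surface of agar".
- **VM.** "Aliquots of dilutions 10^4^, 10^5^, and 10^6^ will be sewn on the surface of Brucella agar".
- **Total streptococci (S).** "Aliquots of dilutions 10^3^ and 10^4^ will be sewn on Mitis Salivarius agar".
- **Mutans streptococci (SM).** Dilutions 10¹ and 10², on the same agar with bacitracin added.
- **Lactobacilli (LB).** "Undiluted aliquots and aliquots from dilution 10^2^ (100 μl) will be pour plated on Rogosa SL agar". This is the only medium on which a step of the series is skipped.
- **After treatment.** Remaining dentin is sampled and "the aforementioned procedures will be repeated", so the same dilutions apply.

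Results are to be CFU of SM and of LB, the percentages S/VM, SM/VM and LB/VM, and the percentage SM/S. The dilution series runs from 10¹ to 10⁶, so a 10¹ and a 10³ tube exist for every sample.

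**The concern.** A 30–300 window spans exactly one factor of ten. Consecutive ten-fold dilutions therefore join without a gap, but skipping one dilution leaves a ten-fold hole. Rogosa agar skips 10¹.

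The lowest dilution plated also sets a floor. Dilutions suited to untreated carious dentin may be too high for dentin that has been drilled, or treated with the gel and light, yet the same ones are used afterwards. VM matters most here because three of the reported percentages divide by it.

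At stake are results tied to a specific objective (the antimicrobial effect on infected dentin, section 3.1.2), in a trial sized on CFU at 16 teeth per group (section 3.1.8). A count lost at the VM floor is lost because it is low, so the missing percentages would depend on the outcome. If residual counts differ between the groups, the losses would differ too.

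**Working it through.** The article states no countable range, so there is no figure of its own to reproduce. The ranges follow from its inputs.

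**Formula.** CFU/ml = colonies × dilution factor ÷ 0.1 ml, evaluated at 30 and 300 colonies.

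| Count | Dilutions plated | Countable range, CFU/ml | Gap |
|---|---|---|---|
| VM | 10⁴, 10⁵, 10⁶ | 3×10⁶ to 3×10⁹ | none |
| S | 10³, 10⁴ | 3×10⁵ to 3×10⁷ | none |
| SM | 10¹, 10² | 3×10³ to 3×10⁵ | none |
| LB | undiluted, 10² | 3×10² to 3×10³ and 3×10⁴ to 3×10⁵ | 3×10³ to 3×10⁴ |

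**LB gap.** A sample at 10⁴ CFU/ml gives 10⁴ × 0.1 = 1,000 colonies undiluted and 1,000 ÷ 100 = 10 colonies at 10². Neither dish may be counted. The 100 µl could be read as applying only to the 10² plate. If the undiluted pour plate were 1 ml (an assumption), it would cover 30 to 300 CFU/ml and the gap would widen to 3×10² to 3×10⁴.

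**VM floor.** 30 × 10⁴ ÷ 0.1 = 3×10⁶ CFU/ml, or 3.8 × 3×10⁶ = 1.14×10⁷ CFU in the 3.8 ml transport tube.

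**Ceiling on percentages.** Highest countable SM or LB ÷ lowest countable VM = 3×10⁵ ÷ 3×10⁶ = 10%. At VM 3×10⁷ it is 3×10⁵ ÷ 3×10⁷ = 1%, and at 3×10⁸ it is 0.1%. The 10% figure does not depend on the aliquot volume if that volume is the same on all plates. S/VM and SM/S are not restricted in this way: their arithmetical maxima are 1,000% and 100%.

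**Share of samples lost.** This cannot be computed from the document. To show the range, assume log10 LB is normal with SD 1 and mean μ. The gap runs from log10 3.48 to 4.48, so the loss is Φ(4.48 − μ) − Φ(3.48 − μ):

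- μ = 2.5: about 14%
- μ = 4: about 38%
- μ = 5.5: about 13%
- μ = 6: about 6%

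The VM floor lies at log10 6.48. With an assumed SD of 1, a post-treatment mean of 6.5 puts about 49% of samples below it, a mean of 7 about 30%, and a mean of 8 about 6%.

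**Dishes planned.** 32 teeth × 2 samples = 64 samples. Nine dilution plates (3 + 2 + 2 + 2) × 64 × 2 duplicates = 1,152.

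**The case against.** The strongest reply is that the article says which dishes are read, not what happens to the others. A laboratory manual may cover dishes outside the window, and such detail need not appear in an article. That stands as regards data handling: the absence of a rule for out-of-range dishes is not held against the plan. It does not remove the point, because the article itself fixes volume, dilutions and window, and these do not reach all the values it intends to report. A sample in the LB gap would show 3 to 30 colonies on its 10² dish. Reading that dish would give a rough value, but only by departing from the stated rule.

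The second reply is that the practical effect is unknown. That also stands. With no expected counts, the loss may be small, and the larger LB percentages above arise when the assumed mean lies inside the gap.

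A reader might go further and infer that the reduction in bacteria will be biased towards the teeth where treatment worked least. The document does not support this. It defines no log reduction, and VM enters the reported results only as a denominator. Loss of VM therefore leaves the SM and LB counts and SM/S untouched. The LB gap lies mid-range with countable values on both sides, can arise before or after treatment, and has no direction of its own. Only losses at the VM floor are tied to low counts, and they affect only the percentages of VM.

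**Conclusion.** The point holds as a matter of assay range; no figure stated in the article is wrong. Following the article as written, LB counts between 3×10³ and 3×10⁴ CFU/ml have no countable dish. VM below 3×10⁶ CFU/ml has no value, so S/VM, SM/VM and LB/VM have none either. SM/VM and LB/VM cannot exceed 10%, and the limit is tighter at higher VM. These results assume 100 µl on every plate and strict use of the 30–300 window; the alternative reading of the Rogosa volume makes the gap wider.

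How many samples are affected is unknown. About 6% to 38% of LB values is an illustration under an assumed SD of 1 log10, not an estimate. Losses at the VM floor would fall on the samples with the lowest counts, but neither the size nor the direction of any bias between groups can be derived from the document. The change is worth making before sampling starts, because an analysis plan cannot supply counts from dishes that were never poured.

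**What to change.** Two additions, both from tubes already in the dilution series:

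1. **Plate the 10¹ dilution on Rogosa agar for all samples.** It covers 30 × 10 ÷ 0.1 = 3×10³ to 300 × 10 ÷ 0.1 = 3×10⁴ CFU/ml, which is exactly the gap. Cost: 64 samples × 2 = 128 dishes.
2. **Plate the 10³ dilution on Brucella agar, at least for post-treatment samples.** The VM floor falls to 30 × 10³ ÷ 0.1 = 3×10⁵ CFU/ml, and the ceiling on SM/VM and LB/VM rises to 3×10⁵ ÷ 3×10⁵ = 100% where it is plated. Cost: 32 × 2 = 64 dishes, or 128 for all samples.

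The total is 192 to 256 extra dishes on 1,152 (about 17% to 22% more), plus the reading time. No extra patient procedure is needed.

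The 100% ceiling applies at the new floor. At higher VM the limit is still set by the upper countable value of 3×10⁵ CFU/ml for SM and LB. Further dilutions are not proposed, since nothing in the document shows that they are needed.
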